#### **- Limitations:**

Selection bias, people who decline to participate in the study can introduce a selection bias, this can be controlled in the data analysis phase, analyzing if there are differences between people who participate and people who do not.

### TRIAL PLAN

The research group will meet to define the instrumental music that will be composed to CF children as an adjunct to each part of CPT routine. After that, the musician member of the research group will compose and score-write the musical pieces. Then, he will interpret these songs playing percussion instruments and record the pieces.

The research group will supervise and select the adequate songs to each part of CPT and then, the musician will edit the musical pieces selected according to the clinical recommendations from the Pulmonology Unit and the Physiotherapist specialist in children CPT.

The music chosen will be compiled in an audio-CD and, after that moment, the recruitment and the intervention will be started and carried out as described above.

Demographic and clinical data will be collected and the questionnaires fill in as mentioned before.

Finally trial data will be analyzed systematically and diffused.

## SCHEDULE

| Tasks                                                       | Year 1 |   |   |   |   |   |   |   |   |    |    |    | Year 2 |   |   |   |   |   |   |   |   |    |    |    |
|-------------------------------------------------------------|--------|---|---|---|---|---|---|---|---|----|----|----|--------|---|---|---|---|---|---|---|---|----|----|----|
| Months                                                      | 1      | 2 | 3 | 4 | 5 | 6 | 7 | 8 | 9 | 10 | 11 | 12 | 1      | 2 | 3 | 4 | 5 | 6 | 7 | 8 | 9 | 10 | 11 | 12 |
| Initial meeting and definition of the music to be developed |        |   |   |   |   |   |   |   |   |    |    |    |        |   |   |   |   |   |   |   |   |    |    |    |
| Music composition/ Music scores-writing                     |        |   |   |   |   |   |   |   |   |    |    |    |        |   |   |   |   |   |   |   |   |    |    |    |
| Interpretation/Recording of musical pieces                  |        |   |   |   |   |   |   |   |   |    |    |    |        |   |   |   |   |   |   |   |   |    |    |    |
| Musical pieces supervising and selection                    |        |   |   |   |   |   |   |   |   |    |    |    |        |   |   |   |   |   |   |   |   |    |    |    |
| Edition of the musical pieces selected                      |        |   |   |   |   |   |   |   |   |    |    |    |        |   |   |   |   |   |   |   |   |    |    |    |
| Study analysis                                              |        |   |   |   |   |   |   |   |   |    |    |    |        |   |   |   |   |   |   |   |   |    |    |    |
| Music-CD compilation                                        |        |   |   |   |   |   |   |   |   |    |    |    |        |   |   |   |   |   |   |   |   |    |    |    |
| Recruitment                                                 |        |   |   |   |   |   |   |   |   |    |    |    |        |   |   |   |   |   |   |   |   |    |    |    |
| Demographic and clinical data collection                    |        |   |   |   |   |   |   |   |   |    |    |    |        |   |   |   |   |   |   |   |   |    |    |    |
| Filled in questionnaires                                    |        |   |   |   |   |   |   |   |   |    |    |    |        |   |   |   |   |   |   |   |   |    |    |    |
| Statistical analysis                                        |        |   |   |   |   |   |   |   |   |    |    |    |        |   |   |   |   |   |   |   |   |    |    |    |

## ETHICAL CONSIDERATIONS

The interventions associated with each group are not related with the use of investigational drugs or devices. The aim of this trial is to compare the usual CPT routine prescribed in CF patients with the use of commercial music or an instrumental music specifically composed, interpreted and compiled to CF children as an adjunct to each part of CPT routine without modifying the usual treatment regimens or programmed clinic visits. This music therapy intervention could help to establish CPT as a positive routine that could improve its adherence and, therefore, the airway clearance. It could maintain the lung function and improve the children's and family member's quality of life.

The safety profile in each group of study: intervention group (music-CD as an adjunct to chest physiotherapy routine), control group without music (usual chest physiotherapy routine) and control group with music (commercial music as an adjunct to chest physiotherapy routine) is favorable, being optimum the benefit / risk balance.

At the end of the trial period, the music-CD will be offered to both control groups (CG and PG participants).

On the other hand, this music therapy intervention does not presents risks for CF participants due to the intervention consists of using the music as an adjunct to usual CPT.

The study will be conducted according to the Declaration of Helsinki and the Spanish and regional protocols concerning to ethics in human research.

The data confidentiality is assured according to the Spanish protection of personal data 15/1999 Law and the basic law 41/2002 that regulates patient autonomy and rights and obligations in terms of information and clinical documentation.

All the researchers involved in the project are committed to preserve the confidentiality of the information provided by participants.

The study has been applied to the Ethics in Human Research Committee of Malaga Regional Hospital "CEI Provincial de Málaga" to be approved.

Participants (children / legal guardian) must have known and understood the purpose of the study and express their agreement by signing the informed consent prior to the inclusion in the study (model attached). The participation is voluntary.

## APPLICABILITY

The music therapy strategy proposed in this project has a direct applicability in healthcare practice due to it is expected an improvement in chest physiotherapy enjoyment and perception, adherence to daily chest physiotherapy, pulmonary symptomatology and quality of life between participants that use specific composed music as an adjunct to chest physiotherapy routine without modifying their treatments and follow-up. These will lead to a reduction in the burden of the disease, which can be translated into improvements in Healthcare systems.

#### ANNEX - CASE REPORT FORMULARY

Age:

Gender:

Respiratory infection exacerbations that requiring hospitalization:

|                                    | Pre-study period | Study-period |
|------------------------------------|------------------|--------------|
| Number of exacerbations            |                  |              |
| Days hospitalized per exacerbation |                  |              |

#### QUESTIONNAIRES:

☐ Chest physiotherapy characteristics:

- Use of activities to accompany the routine (yes /no)
- Type of activities used to accompany the routine (toys, stories, music, radio, TV...)

- ☐ Chest physiotherapy adherence:
  - Routine frequency
  - Number of times per day
  - Interruptions (yes /no)
  - Length per session
- ☐ Chest physiotherapy attitude:
  - Response to the routine using a Likert scale (-3 to +3): least enjoyment – neutral - most enjoyment
  - Feelings about the routine choosing 3 words to describe these feelings
- ☐ Perception of time taken to complete the chest physiotherapy:
  - Perception of being a long routine (yes /no)
  - Time that seems to need the routine
- ☐ About the music:
  - Music use frequency
  - Response to the use of music during routine using a Likert scale (-3 to +3): least enjoyment – neutral - most enjoyment
  - Usefulness of music during routine (yes /no)
  - How music has been useful
  - To continue using this music as an adjunct to the routine in the future (yes /no)
- ☐ Perception of pulmonary symptomatology and impact on quality of life:
  - Measurement of the symptoms of dyspnea using a dyspnea visual analog scale (VAS), being 1 no dyspnea and 7 maximal dyspnea ☐
  - Frequency of respiratory symptoms according to the revised quality of life questionnaire for cystic fibrosis during the previous 2 weeks:

always, often, sometimes, never

Coughing during the day..... ☐ ☐ ☐ ☐

Wake up at night because of coughing..... ☐ ☐ ☐ ☐

To expectorate (spit out the mucus)..... ☐ ☐ ☐ ☐

Mucus appearance: ☐ Watery ☐ Yellow/Transparent ☐ Yellow-Green ☐ Green/Bloody

☐ I do not know

Respiratory congestion..... ☐ ☐ ☐ ☐

Whistling sounds when breathing..... ☐ ☐ ☐ ☐

Breathing difficulties..... ☐ ☐ ☐ ☐

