### **Collaborating researchers:**

[name] [name], PhD. Department of Pharmacology and Pediatrics, Faculty of Medicine, Malaga University. Biomedical Research Institute of Malaga (IBIMA), Malaga, Spain. Unit of Pediatric Pulmonology, Malaga Regional Hospital, Malaga, Spain.

[name] [name]. Physiotherapist specialist in children chest physiotherapy. Department of Pharmacology and Pediatrics, Faculty of Medicine, Malaga University, Biomedical Research Institute of Malaga (IBIMA), Malaga, Spain.

[name] [name]. Professional musician and music teacher of children. Department of Pharmacology and Pediatrics, Faculty of Medicine, Malaga University. Biomedical Research Institute of Malaga (IBIMA), Malaga, Spain. Department of Education. Andalusian Government, Malaga, Spain.

**Objective:** To develop a strategy based on music therapy as adjunct to daily chest physiotherapy in children with cystic fibrosis and to evaluate its effects.

**Study design:** Interventional - randomized controlled trial. Single center: Unit of Pediatric Pulmonology, Malaga Regional Hospital.

**Disease or disorder under study:** Cystic fibrosis.

**Participants:** Children between ages of 2-17 from the Pediatric Pulmonology Unit at Malaga Regional Hospital. The sample size determined in each group is 13 participants. A total of 39 participants are necessary.

**Total study period:** Two years.

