**- Sample size:**

To calculate the sample size, the perception of time taken to complete the routine has been assumed as main variable. According to Grasso et al, (2000) where the control group values in this variable were  $0.2 \pm 10.2$  (mean  $\pm$  SD), considering these values as baseline, a power of 80 %, a confidence level of 95 %, and a similar variability at the end of the study, a difference of 8 minutes would be considered as statistically significant with a sample size of 13 subjects. A total of 39 participants are necessary.

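### The printed questionnaire puts the music evaluation directly before the dyspnea and symptom ratings, which could give the music arms a different rating context from the no-music arm at follow-up

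*Combined protocol and SAP*

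**What the plan says.** The QUESTIONNAIRES part of the annex lists six blocks, and the Study variables section lists the same topics in the same order. The fifth block asks how often music was used, how much it was enjoyed, whether it was useful and in what way. It closes with "To continue using this music as an adjunct to the routine in the future (yes /no". The sixth block then opens with "Measurement of the symptoms of dyspnea using a dyspnea visual analog scale (VAS), being 1 no dyspnea and 7 maximal dyspnea" and goes on to the frequency of cough, expectoration, congestion, wheeze and breathing difficulty.

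The Randomization section defines CG as the arm that uses no music. The Intervention section supplies the study CD to TG only after the baseline questionnaire. It places the second questionnaire at 6 weeks and the final one after a further 6 weeks. The Statistical analysis section compares the response to music between TG and PG only. For change over time it plans a repeated-measures analysis with group and time as factors, and a Wilcoxon test of baseline against final within each group.

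**The concern.** Earlier questions can colour the answers to later ones. A family that has just stated whether and how the music helped may then judge breathlessness or cough with that in mind. The symptom items are self-reports by families who know whether they use music, so masking gives no protection.

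If that prompt is present in two arms and absent in the third, part of any difference in symptoms could come from the form and not from the intervention. Pulmonary symptoms and quality of life are named in the hypothesis and in a secondary objective, so the ratings exposed to this support conclusions that the trial intends to draw.

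**Working it through.** No arithmetic applies. The inputs to the Sample size section (8 minutes, SD 10.2, 13 per group) concern perceived time, and none depends on item order or on the symptom outcomes. The check is to set the sections side by side.

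**Step 1. Order of the form (annex, QUESTIONNAIRES).**

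| Position | Block | Content |
|---|---|---|
| 1 | Characteristics | accompanying activities, and which |
| 2 | Adherence | frequency, times per day, interruptions, session length |
| 3 | Attitude | enjoyment rating, three words for feelings |
| 4 | Perceived time | whether it feels long, how long it seems |
| 5 | Music | use, enjoyment, usefulness, how useful, whether to continue |
| 6 | Symptoms | dyspnea scale, then symptom frequencies |

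Nothing stands between blocks 5 and 6. The documents describe no varied item order, no separate version for CG and no skip rule.

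**Step 2. What each arm can evaluate in block 5 (Randomization and Intervention sections).**

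| Arm | Baseline | 6 weeks and 6 + 6 = 12 weeks |
|---|---|---|
| TG | study CD not yet supplied | composed music, judged just before symptoms |
| PG | assigned use of commercial music not yet begun | commercial music, judged just before symptoms |
| CG | no assigned music | no assigned music |

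The PG baseline entry follows from the order of events in the Intervention section, where the baseline questionnaire comes before the arm-specific routine. For TG the section says outright that the CD comes after baseline.

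**Step 3. Which comparisons are exposed.**

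- TG with CG, and PG with CG: the context differs between arms at follow-up but not by assignment at baseline. A difference of that shape falls on the group-by-time contrast in the planned repeated-measures analysis.
- Baseline with final within TG or PG (Wilcoxon): the context can change between the two visits. In CG it does not change by assignment.
- TG with PG: same items, same place, same visits. The layout builds in no difference.

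**Step 4. Size.** The documents report no test of order effects and give no spread for the symptom items. The size cannot be derived from them. Even the direction is a supposition, although milder ratings after a favourable view of the music is the obvious one.

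**The case against.** The strongest reply is that the annex may be a list of items and not the form as given. It largely repeats the list under Study variables, it lacks question wording, and TG cannot judge the study CD at baseline, so it may simply pool the items for three questionnaires. The documents do not settle this, nor do they say how CG handles the music block. That stands, and the point is therefore conditional. Still, this is the only order the documents give.

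A second reply is that knowledge of the arm is likely to matter more than item order, and that families know what they used before the first question. That also stands. The first block, moreover, already asks whether music or other activities accompany the routine. Reordering removes one avoidable prompt and does not make the ratings masked.

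A reader might go further and infer that asking session length before "Time that seems to need the routine" anchors the trial's main variable. The documents do not support this. Three items separate the two: the enjoyment rating, the three feeling words and the yes/no item on a long routine. The order is the same in every arm and at every visit, so any pull would be common to all arms by design and would more likely dilute a difference than create one. The Sample size section says that "the perception of time taken to complete the routine has been assumed as main variable", but does not define this as a gap between perceived and reported minutes. Reversing the order could let perceived time anchor reported length, which is itself an adherence variable.

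A reader might also want an inflated false-positive rate. That would need an assumed shift in the symptom ratings. No section supplies one, so the result would only restate the assumption.

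**Conclusion.** The point holds as a minor, conditional one. If the form is given in the printed order, and if CG families leave the music block blank, skip it or have nothing to judge in it, the symptom ratings at follow-up come straight after a music evaluation in TG and PG but not in CG. That could add an effect of arm and visit to unmasked self-reports in the comparisons of TG or PG with CG. The comparison of TG with PG, which isolates the composed music from music in general, has no built-in order difference.

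The size is unknown and no figure in the plan rests on it. The documents do not show that symptom ratings are in fact biased or that perceived time is anchored. The case for acting is that the change is free and removes an avoidable difference between arms.

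**What to change.** In the annex, move the music block to the end of the questionnaire, after the dyspnea and symptom items. Do this at all three time points and in all three arms, and leave the other blocks in their current order. Symptoms are then rated before any music evaluation on that form, whatever CG does with the music block.

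The cost before recruitment is one revised page, with no new items, visits or staff. The change should be in place before the first baseline form is collected, because a different order at later visits would itself make the visits less comparable.
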